## 14 Study timeline

| Work                                                                                                                                                                                   | 1st year                              | 2nd year | 3rd year                                                   | 4th year | 5th year |
|----------------------------------------------------------------------------------------------------------------------------------------------------------------------------------------|---------------------------------------|----------|------------------------------------------------------------|----------|----------|
| Clinical work : Consent, patient selection, drug administration, clinical and radiological monitoring for clinical benefit rate, progression and toxicity. Duration : 4.3 years |                                       |          | 3 month block for selection of metronomic dose for stage 2 |          |          |
|                                                                                                                                                                                        | Stage 1                               |          | ↕                                                          | Stage 2  |          |
| Flow cytometry :Endothelial cell suppression ,Duration :4.3 years                                                                                                               | Will be done during Stage 1 & Stage 2 |          |                                                            |          |          |
| Sample collection : Blood sample and tissue collection for biomarkers,Duration;4.3 years                                                                                        | Will be done during Stage 1 & Stage 2 |          |                                                            |          |          |
| ELISA ( done post completion of stage 1 & 2 clinical work, Time duration = 6 months)                                                                                            |                                       |          |                                                            |          |          |

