## 15 Sample size calculation

**Total sample size** : Stage 1 ( 20-30 patients) + Stage 2 ( 76 patients). In stage the continuous reassessment model will be used hence the sample size would be maximum of 30 and minimum around 20. The exact calculations done in both stages are described below in details.

Stage 1 : Flexible-finite sample based approach will be adopted to select the circulating endothelial cells (CEC) interval boundaries and further to use optimum interval design. During the trial, we will continuously update the posterior estimates of decline in CEC and clinical benefit rate and assign patients to the most appropriate dose combination (Figure 1). The Bayesian adaptive screening design will be used to simultaneously select among possible treatment dose combinations. The design is based on formulating the selection procedure as a Bayesian hypothesis testing problem in which the superiority of each treatment combination is equated to a single hypothesis. During the trial conduct, we intend to use the current values of the posterior probabilities of all hypotheses to adaptively allocate patients to treatment combinations. The dose-finding decision will be decided on the twin endpoints the clinical benefit rate at 2 months and proportional decline in CEC at D8 of first cycle. Figure 2 will be used for decision making.

Stage 2: It was assumed that the 3-month progression-free survival (PFS) rate of a standard cancer therapy is 0.50 (H0). An improvement to 0.60 would be considered clinically significant (H1). Assume both the null and alternative PFS distributions follow an exponential distribution. The 1-sided type I error rate of 0.05 and type II error rate of 0.1. Prior assumption includes a fixed enrollment rate of 3 patients per month. We require a stop of 3 months at the end of Stage 1. The library("OptInterim") has been used to calculate the sample size. A 20%extra patient would be taken to account for lost to follow up data. Hence **a total of 76 ( 63 patients +13 patient) sample size is found suitable to carry out the study for stage II with single arm drug therapy.**

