### **20.2 Interim Analysis**

As this is a stage I/II study , interim analysis will be done at after completion of stage 1.

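### Stage 2's stated 5% and 10% error rates are attached to no written decision rule, and the single cohort as written does not deliver 90% power

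*Protocol*

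**What the plan says.** Section 15 of the protocol sets out the Stage 2 hypotheses: "3-month progression-free survival (PFS) rate of a standard cancer therapy is 0.50 (H0") and "An improvement to 0.60 would be considered clinically significant (H1"). It continues: "Assume both the null and alternative PFS distributions follow an exponential distribution". The error rates are given as "The 1-sided type I error rate of 0.05 and type II error rate of 0.1". Two operating inputs follow: "Prior assumption includes a fixed enrollment rate of 3 patients per month", and "We require a stop of 3 months at the end of Stage 1". The calculation is credited to the OptInterim library. The result is 63 patients, plus 13 for loss to follow-up, giving 76. The section gives no first-stage number, look time, stopping boundary or final critical value.

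Section 20.2 states that "interim analysis will be done at after completion of stage 1". No other interim is planned. The chart in Section 14 has a "3 month block for selection of metronomic dose for stage 2" between the two stages.

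Sections 15 and 16.1 base Stage 1 decisions on clinical benefit at 2 months and the fall in circulating endothelial cells, in patients spread over several methotrexate doses. Section 16.1 has Stage 2 end in a Kaplan-Meier median for PFS. Section 20.1 gives the institutional monitoring board oversight of the data, without a stopping criterion.

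**The concern.** Section 15 reads as though a design with an interim look had been used, but the only interim in the protocol falls before the first Stage 2 patient is treated. It cannot act as a look at Stage 2 PFS, because the patients, doses and endpoints all differ. The stated 0.05 and 0.10 are thus not tied to any rule that the protocol describes.

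Two things are at stake. A reader who takes 90% power at face value will read a non-significant Stage 2 as good evidence against the regimen, although such a result may be about as likely as not when the target improvement is real. And no written criterion would end Stage 2 early in a population with a poor outlook: Section 4.2 reports median overall survival of 110 days with metronomic therapy in early failures. At 3 patients per month, 76 patients take 76/3, or about 25 months, to enrol.

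**Working it through.** **Inputs.** All are from Section 15: p0 = 0.50 and p1 = 0.60 at 3 months, exponential PFS, one-sided alpha 0.05 (z = 1.645), power 0.90 (z = 1.282), accrual 3 per month, n = 63 and 76. OptInterim itself was not available to run.

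**The printed figure.** 63 × 1.2 = 75.6, which rounds to 76, so the 20% addition reproduces. The 63 does not:
- Normal approximation on the 3-month rate: n = [(1.645 × 0.5 + 1.282 × √0.24) / 0.10]² ≈ 210. The exact binomial needs 213.
- Exponential test: HR = ln 0.60 / ln 0.50 = 0.737 (medians 3.0 and 4.07 months), |ln HR| = 0.305. Events = [(1.645 + 1.282) / 0.305]² ≈ 92, which is more than either 63 or 76.

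**Power of the cohort as written: exact binomial on 3-month PFS, smallest critical value with alpha at most 0.05.**

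| Patients | Success if progression-free at 3 months | Alpha at 0.50 | Power at 0.60 |
|---|---|---|---|
| 63 | 39 or more | 0.038 | 43% |
| 76 | 46 or more | 0.042 | 51% |

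**Power of an exponential test**, Φ(|ln HR| × √d − 1.645) for d events. The ceiling is every patient progressing:
- d = 63: 0.305 × 7.94 − 1.645 = 0.778, power 78%.
- d = 76: 0.305 × 8.72 − 1.645 = 1.016, power 85%.

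With accrual at 3 per month and analysis 3 months after the last entry, the expected events at p1 are 52.7 of 63 and 65.6 of 76, giving 72% and 80%.

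**Would a two-stage rule rescue 63?** No. At a fixed final sample and critical value, a futility look can only remove successes. A search over two-stage binomial futility designs with a total of 63 and alpha at most 0.05 found a best power of 47%. On a coarse grid, two-stage designs that do reach 90% need a maximum of about 213 to 231 patients.

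**What an optional look would do.** Illustration: stop if 17 or fewer of the first 38 are progression-free at 3 months, with success at 46 or more of 76.

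| True 3-month PFS | Chance of stopping |
|---|---|
| 0.35 | 92% |
| 0.50 | 31% |
| 0.60 | 4% |

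Power at 0.60 goes from 51.25% to 51.17%, and alpha from 0.0423 to 0.0422. While the 38th patient is followed for 3 months, 3 × 3 = 9 more enter, so a stop spares 76 − 47 = 29. The average saving under H0 is 0.314 × 29, or about 9 patients.

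**The case against.** The 3-month stop may be innocent. It matches the dose-selection block in the Section 14 chart, and read that way Sections 14, 15 and 20.2 agree with each other. That stands: the sentence is not firm evidence of a pause inside Stage 2, and what the library computes cannot be established from the protocol. On this reading, though, the stop has no part in the Stage 2 test, and Section 15 still gives no rule for its error rates.

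A reader might infer that the printed rates belong to a two-stage PFS rule that was later dropped. The protocol does not show that: no two-stage binomial rule found with 63 patients comes near 90% power, so a missing look does not explain the gap. Nor is the accrual rate proof of a planned look. Under exponential PFS it governs follow-up and hence events in a single-stage analysis too. With 63 patients analysed 3 months after the last entry, power is 46% with instant accrual, 66% at 6 per month and 72% at 3 per month.

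A single-stage cohort that estimates median PFS is also legitimate, and a futility look is a choice, not a requirement. Individual patients stop protocol drugs at progression (Section 11.1), the board oversees the data (Section 20.1), and ethics reports summarise its reviews (Section 23.1). It would therefore be wrong to say that Stage 2 cannot be stopped; what is absent is a stated boundary. Boundary detail could sit in an analysis plan not seen here. That would not repair a power statement in the protocol that its own inputs do not support.

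**Conclusion.** The point holds in this form. The 0.05 and 0.10 in Section 15 are attached to no written Stage 2 rule, and the only interim in Section 20.2 is not a look at Stage 2 PFS. As written, Stage 2 is a single cohort without a futility boundary. Its power at 0.60 is 43% (63 patients) or 51% (76) on the 3-month rate, and at most about 78% or 85% with an exponential test, against a stated 90%.

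The binomial figures assume that every counted patient has a known 3-month status; those for 76 also treat the 13 patients added for loss as evaluable, which is favourable. The exponential ceilings assume exponential PFS and that everyone progresses. The shortfall appears under both methods, and adding a look does not close it. The case for a look is separate and modest: its main value is if true PFS is well below 0.50, and at 0.50 itself it would continue 69% of the time.

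**What to change.** In Sections 15 and 20.2:
1. State that the end of dose-finding is not an interim of the Stage 2 PFS test, and that the 3-month stop is the dose-selection block, if that is what is meant.
2. Say that Stage 2 is single-stage.
3. Print the test, its critical value and its actual error rates, for example 46 or more of 76 (alpha 0.042, power 51%) or 39 or more of 63 (alpha 0.038, power 43%). If an exponential analysis is intended, name it, keep the accrual rate, and give the follow-up time and expected events.
4. Optionally, add one non-binding futility look for the monitoring board, such as 17 or fewer of the first 38 progression-free at 3 months, and state the error rates for that rule.

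Items 1 to 3 cost only wording, but they bring the low power into the open; keeping 90% for 0.50 against 0.60 would need about 210 patients on the 3-month rate, or about 92 events. Item 4 costs one board review, under 0.1 point of power, and a 4% chance of stopping a regimen that meets the target.

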## 16 Outcome measures

### 16.1 Primary outcome :

In stage I the OBD of methotrexate would be identified using response assessment criteria RECIST version 1.1 and flow cytometry measurement of CEC. So a twin primary endpoints of clinical benefit rate at 2 months ( CR or PR or SD persisting till 2 months) and proportional decline in CEC will be used for determination of OBD.

In stage 2 the PFS would be measured in days from date of recruitment in the study till the date of progression (clinical or radiological or both). Median PFS would be estimated by Kaplan Meier survival method.

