## 2 Summary of proposed research

**Problem statement & rationale :** A combination of platinum based chemotherapy with cetuximab is the recommended palliative chemotherapy regimen in head neck cancers., though less than 1% of patients can afford the treatment in developing countries. As a significantly cheaper alternative, we have designed an oral metronomic chemotherapy (MCT) combination of methotrexate and celecoxib. In a randomized study, we showed a survival advantage along with lower side effects, better QOL and fewer hospital visits compared to single agent cisplatin. One third of failures in head and neck cancers are seen within 6 months, and such patients have median survival of less than 3 months. This MCT was studied in these patients with median expected survival of 4 months (sent for publication). Despite the impressive initial efficacy of MCT, resistance usually develops in 3-6 months. Overexpression of multidrug transporters (Abcc2, Abcc3, and Abcg2 ) may be one of the reason behind the development of resistance to methotrexate used in MCT. Of these, Abcg2 is active in head and neck cancers and over-expressed in 50-60% of patients. Erlotinib (E) an oral tyrosine kinase inhibitor can inhibit Abcg2 mediated drug efflux. In our experience erlotinib when used after failure of cisplatin or MCT results in a promising median survival of 5.06 months.(send for publication). Upfront combination of MCT with erlotinib (MCT-E) studied by the author resulted in a 6 month survival of 80%.(accepted for publication). However these results need confirmation in a large study, along with translational research to identify the mechanism of action, resistance and biomarkers for efficacy prediction.

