Drugs like methotrexate have an anti-angiogenic (metronomic) action when administered at  $\frac{1}{3}$  to  $\frac{1}{10}$  of maximum tolerable dose. We had selected a dose of 15 mg/m^2 for our MCT regimen as it was  $\frac{1}{3}$ rd of the maximum tolerated dose (MTD) . Initial preclinical data suggests that there is a dose range in which this anti-angiogenic action is seen and it is unknown if a lower dose will result in better anti-angiogenic activity. As traditional dose escalation based phase I designs are inappropriate for testing this hypothesis, we have designed a study which would incorporate clinical response and a laboratory biomarker, serum circulating endothelial cells (CECs) to determine the most biologically effective metronomic dose of methotrexate. We aim to utilize CECs as a surrogate serum marker for tumor related angiogenesis for this study.

**Study design and objectives:** This would be a prospective observational single arm study conducted in 2 stages. The primary objective of the first-stage would be to identify the optimal biological effective dose (OBD) of methotrexate in combination with celecoxib ( 200 mg PO BD) and erlotinib (150 mg PO OD).

The primary objectives of the second-stage would be to estimate the median progression free survival (PFS) and overall survival (OS) with the combination of methotrexate used at the OBD with celecoxib and erlotinib.

The secondary objectives would be to evaluate the changes in the profile of serum biomarkers ( VEGF, VEGFR1-3, Tie-2, Angiopoietin -1-2, Thrombospondin 1, Vasoinhibin, Angiostatin, Endostatin ,IL-2,CECs) tissue angiogenic biomarkers (Thymidine phosphorylase, HIF- I-alpha,

DLL, SPARC) and tissue tumor immunity related biomarkers (Foxp3 +ve T reg cells) during the course of MCT. To study the PK/PD of low dose methotrexate.

The tertiary objective would be to study gene expression changes in the tumor tissue during MCT to identify responders and mechanisms of resistance.

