**Study procedures (clinical):** The study population would include patients with chemoresistant oral cancers, fit for MCT-E. In stage 1, a dose de escalation design with continuous reassessment model would be used to identify OBD of methotrexate. The disease control rate at 2 months and the proportional decline in CECs would be used for decision making regarding de escalation. Around 20-30 patients would be required for stage 1. In the second stage the combination of MCT-E would be administered in 76 patients. These patients would be followed at 8th day then subsequently every 30th day till death.

Disease progression would be defined as per RECIST criteria version 1.1. Serum and tissue biopsy would be collected in all patients at baseline prior to the start of MCT-E, at day 8 and at progression. In addition serum samples will be collected at monthly intervals till progression for serial assays of serum biomarkers.

**Study procedures (laboratory):** CECs would be measured in serum by flow cytometry. The other serum angiogenesis related markers would be quantified by ELISA. The tissue tumor immunity and angiogenesis markers would be measured by immunohistochemistry. Microarray would be used to profile the gene expression profile in the tumor specimens. PK/PD would be studied by plasma methotrexate drug level analysis.

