In patients who had failed within 1 month of surgery/ radiation or within 6 months of platinum based systemic therapy who couldn't afford cetuximab we offer metronomic chemotherapy at present. In our retrospective experience ( data sent for publication) in oral cancers when such patients with early failures are subjected to metronomic chemotherapy the median survivals are much below expectations. The median estimated overall survival was 110 days (95% CI 85-134 days). There is an urgent unmet need to modify metronomic schedule so that such likely chemoresistant patients can be effectively treated with a cost effective option.

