### **Followup**

Patients will receive MCT at 4 weekly intervals continuously till progression or intolerable side

As this is a stage I/II trial hence further followup after treatment progression will be conducted as per institutional norms.

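### The Stage 2 primary endpoint is called PFS but is defined as time to progression: Section 16.1 does not make death an event

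*Protocol*

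**What the plan says.** Section 16.1 holds the only definition of the Stage 2 primary endpoint: "PFS would be measured in days from date of recruitment in the study till the date of progression (clinical or radiological or both". It adds that "Median PFS would be estimated by Kaplan Meier survival method". Section 2 ties progression to tumour measurement: "Disease progression would be defined as per RECIST criteria version 1.1".

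The objectives (Sections 2, 3 and 7.1), the hypothesis (Section 6) and the sample size (Section 15) all use the term PFS without saying what counts as an event. No section adds death and none states a censoring rule.

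On prognosis, Section 2 says of patients who fail within 6 months that "such patients have median survival of less than 3 months". For early failures given metronomic chemotherapy, Section 4.2 reports: "The median estimated overall survival was 110 days (95% CI 85-134 days". Section 10.1 admits patients expected to live less than 6 months on standard palliative treatment.

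On follow-up, Section 2 says "These patients would be followed at 8th day then subsequently every 30th day till death", whereas the Followup text in Section 11.2 says "further followup after treatment progression will be conducted as per institutional norms". Section 2 also gives the Stage 2 primary objectives as "to estimate the median progression free survival (PFS) and overall survival (OS").

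**The concern.** Progression-free survival ordinarily ends at progression or death, whichever comes first. Section 16.1 names the date of progression alone. An analyst who followed it to the letter would have no event to record for a patient who dies before progression is documented. In a Kaplan-Meier analysis that patient would leave the risk set without lowering the curve.

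Stage 2 has no control arm that would carry the same distortion. Its hypothesis is a median PFS above 3 months (Section 6), so any upward shift goes straight into the result that is judged.

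**Working it through.** **1. Could the existing wording already cover death?** Section 16.1 accepts clinical as well as radiological progression, so the question is whether clinical progression could include death.
- Section 11.1: after clinical or radiological progression the protocol drugs stop and further treatment follows institutional practice.
- Section 11.6: imaging is done unless the patient has grossly progressed on clinical grounds.

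Both passages describe living patients. Clinical progression therefore does not include death, and the definition as written is time to progression.

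**2. Direction.** The Kaplan-Meier estimate is a product of factors (1 − d/n) over event times. Suppose a patient dies without progression and leaves the risk set on that date. Counting the death as an event puts a factor below 1 into the product. Not counting it removes that factor, and the later risk sets are unchanged. At every time point the curve without the death is therefore equal to or above the curve with it. This strict ordering assumes departure on the date of death. A censoring date at an earlier visit would alter the curve between the two dates, and the protocol does not say which would apply.

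**3. The plan's own figures.** Section 15 sets 3-month PFS at 0.50 (H0) and 0.60 (H1) under exponential distributions.
- H0: hazard λ = ln 2 / 3 = 0.231 per month, median 3.0 months. This agrees with the 3-month threshold in Section 6.
- H1: hazard −ln(0.60)/3 = 0.170 per month, median ln 2 / 0.170 = 4.07 months.

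**4. Illustrative size.** Inputs:
- true PFS at H0 (Section 15);
- exponential hazards (Section 15), with progression and death without progression taken as independent (an assumption);
- f, the share of PFS events that are deaths without documented progression. The protocol does not give f; 5% to 30% is assumed.

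The progression hazard is (1 − f)λ. The recorded 3-month rate is exp(−3(1 − f)λ) = 0.5^(1−f), and the recorded median is 3/(1 − f) months.

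| f | Recorded 3-month rate | Recorded median (months) |
|---|---|---|
| 0 | 0.500 | 3.00 |
| 5% | 0.5^0.95 = 0.518 | 3.16 |
| 10% | 0.5^0.90 = 0.536 | 3.33 |
| 20% | 0.5^0.80 = 0.574 | 3.75 |
| 30% | 0.5^0.70 = 0.616 | 4.29 |

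Setting 0.5^(1−f) = 0.60 gives f = 1 − ln 0.60 / ln 0.50 = 0.263. At about 26% a regimen with no benefit would record the H1 rate.

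**5. Related passages, side by side.**
- *Overall survival.* Section 2 makes it a Stage 2 primary objective together with PFS. The concept sheet (Section 3), Section 7.1 and Section 16.1 name PFS alone, and Section 16 defines no overall survival outcome.
- *Follow-up.* Section 2 follows patients to death. The Followup text leaves the period after progression to institutional practice.

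These two points are separate from the PFS definition. What happens after progression changes neither time to progression nor a PFS that counts death.

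**The case against.** The strongest reply is that this is loose wording of a standard term. The endpoint is called progression-free survival throughout, patients are to be followed to death, and handling of deaths and censoring is often left to an analysis plan, which is not shown. Part of this stands: censoring of deaths is inferred from the definition and stated nowhere. But Section 16.1 is more than silent. It states the end of the interval and leaves out half of it.

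Three stronger readings are tempting, and the protocol does not support them.

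- *The trial and its benchmark measure different things.* Section 15 gives the 0.50 no source and no definition. If it came from data scored in the same way, the two would match.
- *Short survival proves that the bias is large.* What matters is deaths before progression, and median overall survival does not give that share. The 110-day figure (110/30.44 = 3.6 months) comes from metronomic chemotherapy without erlotinib. For the combination, Section 4.4 cites a median PFS of 148 days and 80% survival at 6 months, though it does not say that these were the same kind of early failures. Assessments at day 8, day 30 and then monthly (Sections 11.1 and 12.1), with clinical progression accepted, also make an unrecorded progression before death less likely.
- *The false-positive rate can be stated.* It depends on a test that the protocol does not specify. With 63 patients and true PFS at H0, an exact binomial rule gives 12%, 28% and 53% at f = 10%, 20% and 30%, while an exponential Wald test gives 18%, 46% and 76%. The binomial rule also needs a known 3-month status for every patient, which conflicts with censoring those who die. None of these figures is an estimate for this trial.

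**Conclusion.** The point holds as an error of definition. Section 16.1 labels the endpoint PFS and defines time to progression, and nothing elsewhere corrects it. Under a literal Kaplan-Meier analysis, with patients leaving the risk set at death, the effect cannot work against the regimen.

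The amount is not known. The 3-month rates of 0.52 to 0.62 for f between 5% and 30%, and the crossing of H1 near 26%, rest on an assumed f, independent exponential hazards and true PFS at H0. They show that a moderate share of such deaths would matter. They do not show that this share will occur.

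**What to change.** In Section 16.1, define PFS as the time from recruitment to the first of progression (clinical or radiological) or death from any cause. If a progression-only measure is wanted, name it time to progression and report it as secondary. In Section 15, state whether the 0.50 and 0.60 rates count deaths, and where the 0.50 comes from.

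Separately, reconcile the status of overall survival: either define it as an outcome in Section 16, or remove it from the Stage 2 primary objectives in Section 2. Reconcile also the two statements on follow-up after progression (Section 2 and the Followup text in Section 11.2).

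The cost is a few sentences of protocol text and a PFS estimate that may be less favourable. Section 2 already plans follow-up to death, so the PFS change should need no new data collection.
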